### Outcomes and data collection

2.6

The main outcome of this trial is quality of life related to health, measured by the Functional Assessment of Cancer Therapy – Breast (FACT–B+4) (32); five secondary outcomes related to chronic pain experiences will be also measured: intensity of pain, catastrophising level, pain self-efficacy, kinesiophobia, and fear-avoidance behaviors.

#### The Functional Assessment of Cancer Therapy – Breast+4

2.6.1

The Functional Assessment of Cancer Therapy – Breast (FACT–B+4) (32) is a 41-item instrument designed to measure six domains of quality of life in patients with breast cancer: physical (PWB), social (SWB), emotional (EWB) and functional (FWB), breast cancer subscale (BCS) and lymphedema subscale (ARM). The overall score of the FACT–B+4 ranges from 0 to 148 points (obtained from the sum of the PWB, SWB, FWB and BCS). The score of the PWB, SWB, EWB and FWB ranges between 0 and 28 points, the score of BCS between 0 and 40 points and the score of ARM between 0 and 20 points. In all of them, a higher score translates to a better quality of life. The alpha coefficient (internal consistency) and test–retest reliability for the FACT–B+4 overall score was high (alpha = 0.87; intraclass correlation coefficient: 0.986). This measure has been widely used in breast cancer population previously (33).

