### Sampling method and sample’s size calculation

2.3

For sampling, non-probabilistic convenience and snowball methods will be used. The sample size was calculated based on the change in FACT-B score between the treatment and control groups at week 12. According to a previous study (30), it is estimated that patients in the intervention group would have a difference in FACT-B score of 10.11 points or more compared to the control group (*F*-value = 4.86). This difference is above the minimal important difference reported for this measure (7–8 points) (31) and results in an expected partial Eta2 effect size of 0.049. Considering 2 groups, 4 measurements, a type I risk or α 0.05, type II risk or β 0.20 (study power of 80%) and an estimated dropout rate of 15%, a total of 40 participants (20 per group) are needed to be enrolled. Sample size was calculated using the G*Power software, version 3.1.9.7 (Heinrich-Heine University, Düsseldorf, Germany). Figure 1 shows the flow chart of the study.

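### The scoring rule for the primary outcome contradicts itself: the FACT-B+4 components listed sum to 124, not 148, and no combination of the stated subscale maxima gives 148

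*Protocol article*

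**What the plan says.** Section 2.6 makes this instrument the primary outcome: "The main outcome of this trial is quality of life related to health, measured by the Functional Assessment of Cancer Therapy – Breast (FACT–B+4").

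Section 2.6.1 names its six domains: "physical (PWB), social (SWB), emotional (EWB) and functional (FWB), breast cancer subscale (BCS) and lymphedema subscale (ARM"). It then says that the total "ranges from 0 to 148 points (obtained from the sum of the PWB, SWB, FWB and BCS"). EWB and ARM are not in that list. The subscale ranges follow directly: "The score of the PWB, SWB, EWB and FWB ranges between 0 and 28 points", and "the score of BCS between 0 and 40 points and the score of ARM between 0 and 20 points".

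Section 2.3 uses a slightly different name for the score: "The sample size was calculated based on the change in FACT-B score between the treatment and control groups at week 12". It plans on a difference of 10.11 points and compares this with a benchmark of 7–8 points: "This difference is above the minimal important difference reported for this measure". No other section gives a scoring rule.

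**The concern.** The maximum of a summed score must equal the sum of its components' maxima. Here it does not, and the component list omits a domain that the same section counts as part of the instrument. The text is intact prose, so a broken table or a redaction does not explain the mismatch.

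What is at stake is the definition of the primary endpoint. An analyst who took the component list literally would compute a total without emotional well-being. Section 2.3 gives its planning difference and its minimal important difference for the FACT-B score, and these might not carry over to a shorter composite. Because sections 2.3 and 2.6.1 also name the score differently, a reader cannot be sure which total will enter the group-by-time analysis. A primary score that can be read in more than one way also leaves room to choose between composites after the data are seen.

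**Working it through.** **Inputs, all from section 2.6.1.** Stated maxima: PWB 28, SWB 28, EWB 28, FWB 28, BCS 40, ARM 20. Stated maximum of the total: 148. Stated components of the total: PWB, SWB, FWB, BCS.

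**Step 1: try to reproduce 148 from the listed components.**
28 + 28 + 28 + 40 = 124. The stated figure is not reproduced. The shortfall is 148 − 124 = 24 points, or 24/148 = 16% of the stated maximum.

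**Step 2: try the obvious additions.**

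| Components | Sum of stated maxima | Difference from 148 |
|---|---|---|
| PWB + SWB + FWB + BCS (as listed) | 124 | −24 |
| As listed, plus ARM | 144 | −4 |
| As listed, plus EWB | 152 | +4 |
| All six | 172 | +24 |

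**Step 3: try every other combination.** Any combination consists of k subscales with a maximum of 28 (k from 0 to 4), plus 0, 20, 40 or 60 points from BCS and ARM. To reach 148, 28k must equal 148, 128, 108 or 88. Dividing by 28 gives 5.29, 4.57, 3.86 and 3.14. None is a whole number, so no combination works. The nearest totals are 144 and 152. Changing the list alone therefore cannot repair the section: at least one stated range, or the total, is also wrong.

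**Step 4: what would reconcile it.** Keep 148 and every stated range except that of EWB, and add EWB to the list. EWB then needs a maximum of 148 − 124 = 24, and 28 + 28 + 24 + 28 + 40 = 148. The document does not state the value 24; it is solved backwards from 148. Other single changes also fit the arithmetic. With EWB added, taking 4 points off any one of the other four ranges gives 148. Changing the total to 152 would fit the stated ranges.

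**Step 5: does this reach the sample size?** The inputs in section 2.3 are a partial eta squared of 0.049, two groups, four measurements, alpha 0.05, power 80% and 15% dropout. The range of the score is not among them, so the 40 participants do not depend on this discrepancy.

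**The case against.** The best defence is that this is a reporting slip in the description of a published, cited questionnaire. On that view, EWB fell out of a parenthesis and was grouped with the subscales scored 0–28, while the data will be scored by the instrument's own guide. The section does name EWB as a domain and does give the total as 148. No hypothesis, model, alpha level or timepoint changes. An analysis plan or scoring code that is not shown may already hold the right rule.

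Much of this stands, and it limits what can be concluded. Four stronger readings are tempting but not supported:

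- *The trial will analyse a 0–124 score.* The same sentence fixes the range at 0–148, so the text does not select the shorter score. Nothing shows that the scoring code omits EWB. This is a risk.
- *The EWB range is 0–24.* This follows only if 148 and all the other ranges are right, and the document alone cannot settle that.
- *The 10.11-point difference can be rescaled by the ratio of the two maxima.* A treatment difference does not shrink in proportion to the range of the score, so no converted figure is offered.
- *The omission removes the domain that the programme is most likely to move.* The document gives no effects by subscale.

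The defence does not remove the contradiction. However likely a slip may be, this is the only scoring rule given for the primary outcome, and nothing else in the article corrects it.

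**Conclusion.** The point holds as an internal contradiction in the definition of the primary outcome. The listed components fall 24 points short of the stated maximum, adding EWB as stated overshoots it by 4, and no combination of the stated maxima reaches it.

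The arithmetic alone proves that a stated range or the total is wrong. That the component list is wrong too is a judgement, though a safe one: the list omits a named domain, and it could stand only if the total were 124 or its own ranges were 24 points larger in all.

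The consequences are conditional. If the list were scored literally, emotional well-being would be left out, and the planning difference and minimal important difference in section 2.3 might not apply to the resulting score. The planned enrolment of 40 is not affected. Because the primary endpoint is involved, the correction should be made before analysis, even if it proves to be editorial.

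**What to change.** Before analysis:

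1. Reconcile the component list, the EWB range and the total against the instrument's scoring guide, and state one rule in section 2.6.1. The simplest reconciliation that keeps 148 and the other stated ranges is PWB + SWB + EWB + FWB + BCS with an EWB maximum of 24. Adopt it only if the guide confirms it.
2. State whether ARM lies outside the total.
3. Use the same score name in sections 2.3 and 2.6.1, so that it is clear that the planning difference and the minimal important difference refer to the score being analysed.
4. Check the scoring code against the stated rule and correct it if they differ.

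The cost is a sentence or two of text and a short check of the code. The design, the sample size and the data collection do not change.

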#### Brief Pain Inventory – Short Form

2.6.2

The Modified Brief Pain Inventory – Short Form (BPI–SF) (34) is a 9-item instrument designed to measure pain intensity and pain interference with the daily activities, which has been previously assessed in breast cancer population for this purpose (25, 26). The questionnaire has two subareas, one related to pain intensity, whose score ranges from 0 to 50, with a higher score being an indication of greater intensity; and another related to the interference of pain in activities of daily living, whose score ranges from 0 to 70, with a higher score being indicative of a greater impact on daily life. The internal consistency and the test–retest reliability between dimensions were good (0.87 and 0.89) and low to moderate (0.53 and 0.77), respectively.

#### Pain Catastrophizing Scale

2.6.3

Pain Catastrophizing Scale (PCS) (35) is one of the most widely used instruments to assess the degree of catastrophizing of pain as a result of various pathologies or diseases, including breast cancer population (25, 36). The scale consists of 3 subscales (rumination, magnification and helplessness), whose items will be valued from 0 (nothing) to 4 (all the time) to obtain a total score that ranges from 0 to 52. A higher score translates into a higher level of catastrophizing. The scale has adequate internal consistency (Cronbach’s alpha = 0.79), test–retest reliability (intraclass correlation coefficient = 0.84) and sensitivity to change (effect size ≥2).

#### Pain Self-Efficacy Questionnaire

2.6.4

The Pain Self-Efficacy Questionnaire (PSEQ) (37) is a 22-item instrument designed to measure self-efficacy level related to pain. Each item is scored from 0 to 10. Here, 0 is equal to ‘I think I am totally incapable’ and 10 is equal to ‘I think I am totally capable’. The total score ranges from 0 to 220. A higher score on the questionnaire corresponds to a higher level of self-efficacy. The internal consistency and test–retest reliability between dimensions were 0.91 and 0.75, respectively. This measure has been previously used in cancer survivors with pain (38, 39).

#### Tampa Scale for Kinesiophobia-11

2.6.5

Tampa Scale for Kinesiophobia (TSK-11) (40) is one of the most commonly used to evaluate kinesiophobia in patients with pain, including breast cancer population (36). It is composed of two factors (avoidance of activity and harm) with a total of 11 items that are valued from 1 (totally disagree) to 4 (totally agree). The total score obtained ranges from 11 to 44. More punctuation shows a higher kinesiophobia level. The internal consistency (Cronbach’s alpha = 0.79) found for this scale is good.

#### Fear Avoidance Components Scale Questionnaire – Spanish Version

2.6.6

The Fear Avoidance Components Scale Questionnaire – Spanish Version (FACS – SP) (41) is a questionnaire that allows us to evaluate a patient’s fear of pain and consequent avoidance of physical activity due to fear. The questionnaire consists of 20 items in which a patient rates his agreement with each statement on a 6-point Likert scale. Where 0 = completely disagree and 6 = completely agree. There is a maximum score of 100. A higher score indicates more strongly held fear-avoidance beliefs. Five severity levels are available for clinical interpretation: subclinical (0–20), mild (21–40), moderate (41–60), severe (61–80) and extreme (81–100). It has been previously used in breast cancer population (42).

All outcomes will be assessed at four different timepoints: before intervention (T0), after four-week PNE (T1), after 12-week complete intervention PNE + GEM-Y (T2) and after 3-month of follow-up (T3) (Figure 2). The outcomes will be assessed using the aforementioned validated scales or questionnaires that women will complete by themselves. Moreover, extra information related to their pain context will be collected by two trained evaluators in an online meeting. All data will be collected on a standardized sheet. It will be encrypted and only members of the research team will have access.

**Figure 2 fig2:**
[figure not shown]
SPIRIT schedule.

### Description of the intervention in the experimental and control group

2.7

An online focused-person therapeutic program, a more up-to-day modality for this type interventions (43), that combines PNE and GEM-Y will be implemented in the experimental group. The sessions will be applied in groups of 10–15 participants, with 3 months being the duration of the entire program. The program will have two parts: the first will involve 8 sessions of PNE during the first month (2 sessions each week, 1 h/session), while the second will involve the use of 16 sessions of GEM-Y during the following 2 months (2 sessions each week, 1 h/session). Figure 3 shows an overview of the experimental intervention.

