**Figure 4 fig4:**
[figure not shown]
Overview of the PNE sessions.

GEM-Y sessions will be organised into four phases: theoretical content of the session, ‘pranayama’ or breathing exercises, ‘dhyana’ or guided meditation, and ‘asanas’ or postures and movements. Moreover, each session will focus on a different part of the body. In this way, yoga is used as a method of therapeutic exercise together with movement representation techniques (44, 45). The program will be delivered by a trained therapist following the principles of progression, gradualness and individualisation proposed by “Twin Peaks” metaphor (22). Thus, at the beginning of the sessions each participant must identify their pain baseline in order to apply an optimal dose of exercise (principle of individualisation). Instructions are given to the participants so that they can always adapt the level of effort to their needs and their progression (more functionality with less associated pain). With regard to the principles of progression and gradualness, since each participant will have a different starting point at the beginning of the programme and will move to their own level, the rate of progression of each participant must also be different. The intensity of the proposed exercises will be progressively adapted to the needs of the group by varying the following parameters: complexity of the ‘asanas’, volume of work (number of exercise blocks and repetitions), control of the relationship work time - rest time ratio. To identify the needs and progress of the group we will use the feedback collected from the participants at the end of each session, and the weekly pain diaries. A more detailed description of the GEM-Y sessions can be found in the Supplementary material.

The whole intervention will be implemented online using the videoconference platform of the University of Seville. Furthermore, WhatsApp and e-mail will be used during the study to give information, provide material or answer queries. Participants’ attendance will be recorded, along with the reasons for non-attendance.

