### Method for data analysis

2.8

The statistical processing of the data will be conducted with the PASW Advanced Statistics, version 26.0 (IBM Corp, New York, NY, United States). Intention-to-treat principles will be considered for all analyses. The normal distribution of the variables will be assessed with the Shapiro–Wilk test. Descriptive data will be reported as mean (standard deviation), median (interquartile range Q_3_–Q_1_) or in percentages. Baseline homogeneity will be tested with Chi-square or Fisher’s exact tests; student’s t test or Mann–Whitney *U*-test.

In those variables in which the 4 measurements are adjusted to normality in both groups, a mixed-model analyses of variance ANOVA (2 × 4) will be used to differences in the outcomes after intervention, with group (PNE + GEM-Y or control) as a between-subject factor and time (the different measurements performed) as a within-subject factor. The hypothesis of interest will be the interaction group by time with an *a priori* alpha level of 0.05. Partial eta squared (η2) will be calculated to estimate the effect size. If any of the measurements do not adjust to normality, we will use the Friedman ANOVA test and the effect size will be calculated as Rosenthal’s r with the formula: *r* = Z/√N. All statistical tests will be performed considering a confidence interval of 95%.

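### Treatment in about two therapy groups is ignored in the sample size and the 2 × 4 ANOVA; if outcomes correlate within those groups, the false-positive rate exceeds 5% and the 80% power holds only under zero correlation

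*Protocol article*

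**What the plan says.** - **Delivery (2.7).** The experimental arm attends 24 live online sessions: 8 of pain education, then 16 of graded movement. On format: "The sessions will be applied in groups of 10–15 participants". On the movement sessions: "The intensity of the proposed exercises will be progressively adapted to the needs of the group". That adaptation uses participants' feedback and weekly pain diaries.
- **Control arm (2.7).** Controls receive biomedical information and a booklet. No group sessions are described.
- **Sample size (2.3).** The calculation starts from a published result that "results in an expected partial Eta2 effect size of 0.049". With two arms, four measurements, alpha 0.05, 80% power and 15% dropout, "a total of 40 participants (20 per group) are needed to be enrolled". No allowance for correlation within therapy groups is listed.
- **Analysis (2.8).** The model is a 2 × 4 mixed ANOVA "with group (PNE + GEM-Y or control) as a between-subject factor and time (the different measurements performed) as a within-subject factor". The group-by-time interaction is the hypothesis of interest. If normality fails, a Friedman test is used.

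**The concern.** Women in one therapy group share peers, sessions and an exercise intensity set for that group, so their outcomes may be more alike than those of women in different groups. The sessions begin after T0. Any shared effect therefore appears only at T1–T3 and only in the experimental arm. It does not cancel against baseline; it adds directly to the group-by-time interaction, which is the primary test.

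The planned ANOVA takes its error term from variation between individual women and does not see variation between therapy groups. At stake are intervals that are too narrow, a false-positive rate above the stated 0.05, and a power figure whose independence assumption is not disclosed.

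**Working it through.** **Inputs from the article.** Partial eta squared 0.049; 2 arms; 4 measurements; alpha 0.05; power 80%; dropout 15%; 40 enrolled, 20 per arm (all 2.3); therapy groups of 10–15 (2.7). Twenty women fit that range only as 10 + 10.

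**Assumptions.** The article gives no ICC, no correlation between repeated measurements (rho) and no nonsphericity value (epsilon). ICC is taken as 0.01, 0.05 and 0.10.

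**1. Reproducing the stated 40.** For the within–between interaction, f² = 0.049/0.951 = 0.0515.
- rho 0.4, epsilon 1: with N = 34, lambda = 0.0515 × 34 × 4/0.6 = 11.7 on 3 and 96 df, so power is 81.2%. Then 34/0.85 = 40.
- rho 0.5, epsilon 0.75: with N = 34, power is 80.3%, which also gives 40.
- rho 0.5, epsilon 1: N = 28 suffices, and 28/0.85 rounds up to 33, which does not match.

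So 40 is reproduced, with all women independent.

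**2. Standard error of a simple arm difference.** With 17 analysed per arm, mean group size is m = 17/2 = 8.5. Only one arm is clustered, so the variance ratio is [1 + 1 + (m − 1) × ICC]/2 = (2 + 7.5 × ICC)/2.

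| ICC | Variance ratio | SE factor | Type I error, 2 × P(Z > 1.96/factor) |
|---|---|---|---|
| 0.01 | 1.0375 | 1.019 | 5.4% |
| 0.05 | 1.1875 | 1.090 | 7.2% |
| 0.10 | 1.375 | 1.173 | 9.5% |

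**3. The planned interaction test.** This was simulated with 17 per arm, therapy groups of 9 and 8, rho 0.4 (compound symmetry), and a group effect on T1–T3 in the experimental arm only. The treatment effect was either constant over T1–T3 or building up to T2. ICC is the share of total variance.

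| ICC | Type I error | Power, test as planned | Power, test held at a true 5% |
|---|---|---|---|
| 0 | 5% | about 82% | about 81% (exact, step 1) |
| 0.01 | about 5% | about 81% | about 80% |
| 0.05 | 6–7% | 78–80% | about 75% |
| 0.10 | 8–9% | 76–79% | about 70% |

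The planned test keeps most of its power because it rejects too easily. The last column shows what is lost once the level is restored.

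**4. A shortcut that overstates the loss.** Dividing lambda by the variance ratio gives 11.7/1.0375 = 11.3, 11.7/1.1875 = 9.8 and 11.7/1.375 = 8.5, hence powers of 80%, 73% and 66%. These describe a level-corrected test, not the planned one. They also inflate all three interaction degrees of freedom, whereas a common shift over T1–T3 affects only one direction.

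**The case against.** **The ICC may be close to zero.** Section 2.7 also says that each woman works at her own level and progresses at her own rate, and delivery is online. It refers to one trained therapist. If that person leads both groups, therapist and core content are common to the whole arm and add no variance between groups. This stands: peers and group-level adaptation remain as sources, and at ICC 0.01 the effect is negligible.

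**Power might not drop below 80%.** With rho 0.5 and epsilon 1, 34 analysed women would have 88% power, and even the shortcut in step 4 leaves about 82% at ICC 0.05 (m = 8.5). That is correct, but those settings do not give the stated 40.

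**Controls may not be independent either.** Their independence is inferred from the absence of group sessions. Snowball recruitment (2.3) could correlate women in either arm. This stands as a limit on the figures.

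**Two clusters cannot be modelled.** They leave one degree of freedom for between-group variance, so a random effect could not be estimated reliably. This stands, and none is asked for. It does not justify a power figure that leaves the zero-correlation assumption unstated.

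**A condensed article may leave this to the analysis plan.** A sensitivity analysis may indeed sit there. But the article itself fixes the power inputs and the model factors, and both rest on independence that its own delivery section puts in doubt.

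**Conclusion.** The concern holds conditionally. Any positive within-therapy-group correlation makes the planned standard error too small and the type I error higher than 5%: about 5%, 6–7% and 8–9% at assumed ICCs of 0.01, 0.05 and 0.10. These sizes rest on 17 analysed per arm, two therapy groups, independent controls and rho 0.4, none of which the article states outright.

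Two stronger readings are not supported. A reader might infer that the planned test's power falls to 73% or 66%; as planned and uncorrected, it stays at about 76–81%, and a test held at a true 5% has about 80%, 75% and 70%. A reader might also infer that clustering is established, or that the ANOVA must be replaced. The article gives no ICC, and its individualised delivery could keep it small.

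**What to change.** 1. **Section 2.3:** state that the 80% power assumes no correlation within therapy groups, and give the level-corrected power for ICC 0.01, 0.05 and 0.10 (about 80%, 75% and 70% under the assumptions above). State the rho and epsilon used.
2. **Data collection:** record each woman's therapy group. Session attendance is already recorded, so this is one added variable.
3. **Section 2.8:** prespecify a sensitivity analysis on one named contrast, the arm difference in T0-to-T2 change in FACT-B+4. The three-df interaction and the Friedman fallback have no single standard error to inflate, so the contrast must be named. Multiply its standard error by sqrt((2 + (m − 1) × ICC)/2), with m the mean analysed therapy-group size and ICC defined for the change score, at 0.01, 0.05 and 0.10. Report beside the primary result whether the conclusion holds. The formula assumes roughly equal arms and variances.

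The ANOVA stays primary. If the analysis plan already contains such an analysis, the article need only refer to it. The cost is one variable, a few lines of text, a less favourable power statement, and a wider sensitivity interval that rests on assumed ICCs rather than trial data.
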